## Abstract

**Background:**

Non-adherence to immunosuppressive therapy is a prevalent risk factor for poor clinical and after kidney transplantation (KT), and has contributed to the lack of improvement in long-term graft survival over the past decade. Understanding the multilevel correlates and risk factors of non-adherence is crucial to determine the optimal level for planning interventions, namely at the patient, health care provider, KT centre, and health care system level. Brazil, having the largest public transplantation program in the world and with regional differences regarding access to health services and service implementation, is in a unique position to study this multilevel approach. Therefore, the Adhere Brazil Study (ADHERE BRAZIL) was designed to assess the prevalence and variability of non-adherence to immunosuppressants and to health behaviours among adult KT recipients in Brazil, and to assess the multilevel correlates of non-adherence to immunosuppressive medication. We describe the rationale, design, and methodology of the ADHERE BRAZIL study.

**Methods/Design:**

This is an observational, cross-sectional, multicentre study that includes 20 Brazilian KT centres. A stratified sampling approach is used, based on strata, with the following characteristics considered: geographical region and transplant activity (number of KTs per year). A random sample of patients (proportional to the size of the centre within each stratum) is selected from each centre. The prevalence of different health behaviours is assessed through self-report. The assessment of multilevel correlates of non-adherence is guided by the ecological model that considers factors at the level of the patient, health-care professional, and transplant centre, using established instruments or instruments developed for this study. Data will be collected over an 18-month period, with information obtained during the regular follow-up visits to the transplant outpatient clinic and directly entered into the Research Electronic Data Capture (RedCap) system. Data entry is performed by a trained professional who is part of the transplant team. The data collection began in December 2015.

**Discussion:**

This multicentre study is the first to evaluate multilevel correlates of non-adherence in KT patients and will provide a reliable estimate of non-adherence in Brazilian KT patients.

**Trial registration:**

ClinicalTrials.gov on 10/10/2013, NCT02066935.

**Electronic supplementary material:**

The online version of this article (10.1186/s12882-018-0840-6) contains supplementary material, which is available to authorized users.

## Background

Kidney transplantation (KT) is the renal replacement therapy that provides a better quality of life and longer survival [1, 2]. However, the long-term graft outcome has not improved over the last decade, and remains an important clinical problem [3, 4]. Non-adherence to immunosuppressive therapy is a prevalent risk factor for this worse outcome in KT and consequently contributes to the lack of improvement in the long-term graft survival [5–7]. Assessing the correlates and risk factors of non-adherence is crucial to guide intervention development, i.e. interventions needed at patient, health care providers, KT centres or health care system level [5, 6, 8, 9].

The World Health Organization defines adherence as a multidimensional process that involves factors related to the following: socioeconomic profile (family income, social support, cost of medications), the characteristics of the disease and its treatment (comorbidities, chronicity of the disease, complexity of regimen), the patient as an individual (self-efficacy, health beliefs, health literacy), the health care professionals involved in the treatment, and the health care system [10]. However, in transplantation, as in other chronic diseases, most studies have focused only on the socioeconomic, disease- and treatment-related factors [5, 8, 10, 11]. A meta-analysis of 29,000 KT patients, performed in the modern era of immunosuppressive therapy, reported that non-adherence was explained only in part by the factors included in the study. The authors suggested that other factors, potentially linked to higher levels of care (i.e. health care team organization and health care system), also needed to be considered in order to understand patient non-adherence [11]. This view is reflected by the ecological model shown in Fig. 1, which posits that a patient’s behaviour results from multilayered influences at the level of the health care provider (micro), health care organization (meso) and health care system and policies (macro) [9, 12]. For instance, it has been shown that practice patterns that apply better principles of chronic illness management (CIM) are associated with favourable clinical and health care utilization outcomes in chronically ill populations [13]. Two studies had found similar results in KT patients [14, 15]. KT can be defined as a chronic disease as transplant patients are dependent on lifelong therapy and follow-up. Moreover, KT requires active patient participation in specific health behaviours to improve outcomes, such as: medication taking, maintenance of regular physical activity, reduction/cessation of alcohol intake, protection from ultraviolet sun, cessation of smoking or maintenance of a non-smoking status, and keeping medical appointments [16, 17].

**Fig. 1 Fig1:**
[figure not shown]
Ecological model used, adapted from Bronfenbrenner et al., [12] and Berben, [9] (with permission)

To date, only one study has comprehensively addressed the multilevel factors associated with non-adherence to immunosuppressive drugs among 1680 heart transplantation recipients, in 36 centres across 11 countries and 4 continents - The BRIGHT Study (Building Research Initiative Group: Chronic Illness Management and Adherence in Transplantation). The BRIGHT study also mapped practice patterns related to CIM in heart transplantation [18, 19]. Such elaborate data is lacking for KT and could contribute to identify leveraging points for adherence interventions.

Our group has recently evaluated selected multilevel correlates in a single centre study involving patients after the first year post-KT, in Brazil. Non-adherence to immunosuppressive therapy was identified in half of the patients. Surprisingly, a better economic profile, reflected by a higher family income, was the only variable that correlated to non-adherence. Given the inclusion of a single centre, meso level factors, such as practice patterns during post-transplantation follow-up, could not be evaluated [20].

Although non-adherence is a frequently reported behaviour in KT recipients, its prevalence varies according to the method of diagnosis, operational definitions used, and sampling method [5, 6, 11]. Adherence is defined as an agreement between a patient’s behaviour and the prescribed treatment, including the extent to which a patient takes medications, follows a diet, and/or implements lifestyle changes as prescribed by health care providers [10]. In transplantation, while studies have largely focused on adherence to immunosuppressive therapy [21], less attention has been given to adherence to other health behaviours [11]. The prevalence of non-adherence to prescribed immunosuppressive regimen among KT recipients ranges between 19 and 25 cases per 100 patients per year (PPY) [11]. Consequences of non-adherence are serious, including more acute rejection episodes, worse graft function and reduced survival, greater morbidity, and greater costs to the health systems [5, 6, 8, 22–26]. In the absence of a gold standard method to assess non-adherence to immunosuppressive therapy, a combination of methods is preferred to maximize the sensitivity of the assessment [27]. However, only a few studies have evaluated adherence to immunosuppressive therapy applying this methodology [20, 28, 29].

Adherence to other health behaviours after KT has been much less studied. The prevalence of smoking ranges from 2.8 to 4.0 PPY (median, 3.4 PPY) [11], and has been associated with cardiovascular diseases and higher mortality [30]. Less than two KT patients per 100 PPY are reported as not limiting/quitting alcohol consumption [11], but it is not clear if alcohol consumption is a risk factor for worse allograft and patient survival [31, 32]. Non-adherence to physical activity is prevalent, at 21.8 cases per 100 PPY [11, 33, 34]. Exercise interventions showed positive effects on intermediate outcomes, such as higher aerobic capacity and muscle strength; however, strong evidences on improved mortality and graft survival do not exist [34, 35]. One study reported non-adherence to medical appointments to be low among KT patients, at 4.7 cases per 100 PPY, with no association with worse outcomes [11].

Brazil is in a unique position with regard to KT, ranking second worldwide, in the absolute number of KTs performed and having the largest public transplantation program. However, regional discrepancies in transplant activity exist in Brazil, due to differences in regional population density, human development index, and the number of transplant services and trained professionals available. The largest proportion of KT activity is concentrated in the South and Southeast regions of the country and in large transplant centres with high transplant activity [36–39]. These regional differences, within the same country and under the same health care system, provide a valuable opportunity to explore how differences in service implementation and access to health services can influence non-adherence after KT. To date, only a few Brazilian studies have evaluated the prevalence of non-adherence to immunosuppressive therapy and health behaviours after KT [20, 40–47].

The ADHERE BRAZIL study aims to explore these gaps, specifically the prevalence of non-adherence to different health behaviours in the Brazilian KT population, considering the potential differences in access and challenges of the Brazilian Health Care System and also performing a broad evaluation of multilevel correlates to non-adherence to immunosuppressive therapy, including factors at the level of patients, health care providers, health care services, and health policies. Involving centres from all national regions and with different patterns of transplant activity will provide us with the valuable opportunity to benchmark patient non-adherence to KT treatment, characterize differences in patterns of clinical practice that may be associated with non-adherence, and a rare opportunity to share experiences among centres.

## Methods/Design

The aims of the ADHERE BRAZIL study are as follows: 1. To estimate the prevalence of non-adherence to immunosuppressants, and to other treatment-related aspects (smoking cessation, alcohol consumption, physical activity, and appointment keeping), in KT recipients among different KT centres across different regions of Brazil; 2. To explore multilevel factors associated to immunosuppressive adherence at the level of patient (socio-demographic, clinical), healthcare provider (patient satisfaction with the interpersonal dimension of care, trust in the transplant team, social support), healthcare organization (composition of the team, operational access, CIM transplant program practice patterns), and healthcare system and policies (perceived financial burden of the treatment regimen, insurance status, barriers to access to the immunosuppressive drugs, Brazilian region); and 3. To benchmark the participating centres, regarding their practice patterns that are associated with non-adherence to health behaviours after KT.

### Study design

The ADHERE BRAZIL study is a multicentre, national, cross-sectional, observational study, based on survey design. The methodology is derived from the BRIGHT study [18].

### Sampling design and setting

A convenience sample of 20 centres was identified for inclusion, using a stratified sampling strategy. In Brazil, the KT activity of a centre is strongly associated with its geographical regions and its regional economic development. High activity centres are concentrated in the South and Southeast regions of the country, with low/moderate activity centres being more prevalent in the North, Northeast, and Midwest regions. To ensure an adequate representativeness from the enrolled centres, we defined four strata of equal size (approximately 283 patients): North, Northeast and Midwest with low or moderate activity; South and Southeast with low activity; South and Southeast with moderate activity; and South and Southeast with high activity. In each stratum, the number of patients in each centre is proportionally defined by the number of patients being followed up. The inclusion criteria for centres were as follows: performance of ≥10 KTs per year over the 5-year period preceding the study (2010-2014) and a signed agreement provided by the centre’s director. The 20 centres participating in the study are listed in Table 1, with their geographical distribution shown in Fig. 2. The majority of centres were located along the coast, following the same distribution as large- and medium-sized Brazilian cities [48].

**Table 1 Tab1:** Participating centres of the ADHERE BRAZIL Study, divided by Brazilian geographical regions and transplant activity

Centre	Brazilian region	Transplant activity ^a^
Hospital Ophir Loyola – Belém/PA	North	Low
Hospital Universitário do Maranhão – São Luiz/MA	Northeast	Low
Hospital Antônio Targino Ltda. - Campina Grande/PB	Northeast	Low
Hospital Universitário Onofre Lopes - Natal/RN	Northeast	Low
Hospital Universitário Walter Cantídio – Fortaleza/CE	Northeast	Moderate
Hospital Universitário de Brasília – Brasília/DF	Midwest	Low
Centro Estadual de Transplantes/Hospital São Francisco de Assis na Providência de Deus - Rio de Janeiro/RJ	Southeast	Moderate
Fundação IMEPEN/Hospital Universitário da Universidade Federal de Juiz de Fora – Juiz de Fora/MG	Southeast	Low
Fundação Osvaldo Ramos - Hospital do Rim e Hipertensão/UNIFESP – São Paulo/SP	Southeast	High
Hospital Israelita Albert Einstein – São Paulo/SP	Southeast	Moderate
Hospital São João de Deus – Divinópolis/MG	Southeast	Low
Hospital das Clínicas da Universidade Estadual de Campinas/Unicamp – SP	Southeast	Moderate
Hospital das Clínicas de São Paulo – São Paulo/SP	Southeast	High
Instituto de Urologia e Nefrologia - Hospital de Base São José Rio Preto – São José do Rio Preto/SP	Southeast	Low
Santa Casa de Misericórdia de Belo Horizonte – Belo Horizonte/MG	Southeast	Low
Santa Casa de Misericórdia de Juiz de Fora – Juiz de Fora/MG	Southeast	Low
Fundação Pró Rim/Hospital Municipal São José – Joinvile/SC	South	Moderate
Hospital Angelina Caron – Curitiba/PR	South	Low
Hospital das Clínicas de Porto Alegre – Porto Alegre/RS	South	High
Santa Casa de Porto Alegre – Porto Alegre/RS	South	High

^a^ Volume of transplants performed: low activity, < 50 KTs/year; moderate activity, 50 to 150 KTs/year; and high activity ≥150 KTs/year

**Fig. 2 Fig2:**
[figure not shown]
Location of centres participating in the study. Transplant activity is indicated in colour, as follows: Red, high activity (> 150 kidney KTs/year); green, moderate activity (50 to 150 KTs/year); blue, low activity (< 50 KTs/year)

KT patients are randomly selected using a computer-generated list (Blockrand package for R language) and screened according to the following inclusion criteria: recipient of single and first KT; age > 18 years; > 1-year post-transplant; and ability to understand the objectives of the study. Patients are excluded if the immunosuppressive regimen is only based on drugs for which the blood monitoring is not available or not covered by Brazil’s health care system, e.g. mycophenolates without calcineurin or proliferation signal inhibitors. Patients randomly selected and meeting our inclusion criteria are invited to participate during their routine medical consultation visits, and those providing written informed consent are enrolled.

Using the OpenEpi stats program, the sample size was calculated for studies of population prevalence. Population size was defined based on data from the 2012 Brazilian Registry of Transplant (RBT 2012) available through the Brazilian Association of Transplantation [49]. Of the 57,815 patients who received a KT in Brazil from 2000 to 2012, we only considered the 31,241 patients registered to be under follow up in RBT 2012 as eligible for our calculation. Based on a non-adherence prevalence rate of 50%, the 95% confidence interval with a 5% sample error, and a design effect of 3.0, a sample size of 1139 patients was calculated and, considering the multi-stage design of the study, divided into approximately 283 patients in each stratum.

The number of patients included by each centre, considered as clusters in the analysis, is proportional to the number of transplants performed per year and the number of patients in follow-up, so called the size of the KT centre. According to the RBT 2012, there were 123 active transplant centres in Brazil, distributed across 22 states, which performed 5385 KTs in that year [49]. Due to the absence of an official classification of KT centres based on their activity, we proposed the following classification, which is based on a pre-existing classification for heart transplantation [18], and taking into consideration the profile of the centres included in the study: low activity, ≤50 KTs/year; moderate activity, 50-150 KTs/year, and high activity, ≥150 KTs/year. We used the 5 years prior to the study period (2010 to 2014) as the reference period for the KT activity of a centre. Our classification was validated by consulting specialists through a web survey, with 92% of respondents considering our proposal as either ‘adequate’ or ‘very adequate’.

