##### Healthcare system and policy level (Macro level)

For KT patients, the Brazilian Public Health System offers outpatient follow-up, immunosuppressive drugs, laboratory exams, and hospitalizations. As the public system is sometimes inefficient in providing access to the required exams and to hospitalization, some individuals do choose to pay for a complimentary private health insurance. Self-reported financial burden is assessed by identifying the complimentary private health insurance status [20]. City and region specific data related to health care access, such as number of hospitals and the number of intensive care beds available, and relevant information about the transplant centre are retrieved from the 2012 RBT [49], as summarized in Additional file 1: Table S2.

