To explore the association between medication non-adherence and multilevel studied correlates, the analyses will follow the multilevel ecological model, following the hierarchical approach [70]. This approach is a forward driven variable selection method, based on the epidemiological framework adopted, following the proximity of the variable levels to the patient in a theoretical causal framework. The non-adherence indicator (binary) variable will be analysed using generalized estimation equations (GEE). This population average approach is an adequate modelling framework that can handle the multistage nature of the study design, as well as provides flexibility regarding the probability distribution adequate to each outcome variable nature, and consequently the association parameter to be estimated. For instance, binary outcomes, such as non-adherence, will be modelled using the Poisson distribution and the log link function, providing prevalence ratios as association parameter. Discrete or count outcomes, like absence at scheduled follow-up consultations, can also be modelled as a Poisson or Negative Binomial distribution with log link function, but providing a counting rate ratios as the association parameter. Association effects will be considered of scientific relevance on the basis on their magnitude (effect size), precision (by their 95% CI) and associated *p*-value. As per the recent statement from the American Statistical Association, terms such as ‘statistically significant and model adjustment based only on p-values’ will no longer be adopted in the analysis [71].

All analyses will be performed using IBM Statistics (SPSS 24.0, Chicago, IL, USA) and STATA (version 14, StataCorp LP, College Station, TX, USA) statistical packages. All codes used will be publically available, permitting reproducibility.

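### City-level factors are modelled with the centre as the cluster, yet the 20 centres lie in only 16 cities; their intervals will be too narrow if non-adherence stays correlated within a city

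*Protocol article*

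**What the plan says.** Sampling design and setting (protocol article) names the cluster: "The number of patients included by each centre, considered as clusters in the analysis". The same section gives the number of units: "A convenience sample of 20 centres was identified for inclusion, using a stratified sampling strategy".

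The section on the healthcare system and policy (macro) level, which stands under the multilevel correlates of medication non-adherence, adds "City and region specific data related to health care access, such as number of hospitals and the number of intensive care beds available" and refers to Table S2 of the additional file for details.

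For Aim 2, the statistical analysis plan section says "The non-adherence indicator (binary) variable will be analysed using generalized estimation equations (GEE", with a Poisson distribution and log link giving prevalence ratios. It adds: "This population average approach is an adequate modelling framework that can handle the multistage nature of the study design". The intervals carry weight in the reading of results: "Association effects will be considered of scientific relevance on the basis on their magnitude (effect size), precision (by their 95% CI", together with the p-value.

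Table 1 lists each centre with its city, for example "Hospital das Clínicas de São Paulo – São Paulo/SP". No city level, city cluster or allowance for centres sharing a city is mentioned anywhere in the article.

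**The concern.** A GEE with a robust variance clustered on centre takes centres as independent of each other. A factor measured on the centre's city has the same value in every centre of that city, so it varies at a level above the stated cluster. Any remaining influence that centres in one city share goes directly into the coefficient of the city factor, and a variance built from centre totals does not capture it.

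The study's premise is that local access to services shapes adherence, so a shared city influence is plausible. At stake are the intervals and p-values for the city-level factors, which would claim more replication than the sample contains. Prevalence estimation in Aim 1 is not part of this point.

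**Working it through.** **1. The plan's own figure.** Inputs from Sampling design and setting: N = 31,241, p = 0.5, d = 0.05, design effect 3.0.

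n = DEFF × N × p(1−p) / [(d²/z²)(N−1) + p(1−p)] = 3 × 31,241 × 0.25 / [(0.0025/3.8416) × 31,240 + 0.25] = 1138.5, which rounds up to the stated 1139. The article gives no precision figure for city-level factors.

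**2. Count of cities (Table 1).** São Paulo has 3 centres, Porto Alegre 2 and Juiz de Fora 2, making 7. The other 13 are each alone in their city (the Unicamp centre taken as Campinas). Cities: 3 + 13 = 16.

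**3. Share of patients.** Each of the four strata has about 283 patients, a total of 4 × 283 = 1132. By Table 1 the strata hold 6, 6, 4 and 4 centres. Assuming equal centre sizes within a stratum, a centre has 283/6 = 47.2 or 283/4 = 70.75 patients.

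- São Paulo: 3 × 70.75 = 212
- Porto Alegre: 2 × 70.75 = 141.5
- Juiz de Fora: 2 × 47.2 = 94.3

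Sum 448; 448/1132 = 39.6%. All four South/Southeast high-activity centres lie in São Paulo or Porto Alegre.

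**4. Assumed ICC.** Size-weighted mean cluster size Σm²/Σm = 58.96. Attributing the whole design effect of 3.0 to clustering, ICC = (3 − 1)/(58.96 − 1) = 0.0345.

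**5. Coverage with a small-sample correction.** Simulation of a Poisson log-link model with one city-level covariate, prevalence 50%, delete-one-cluster jackknife, and t limits on G − 2 df (18 for centres, 14 for cities). The documents do not give the city share of the between-centre variance, so a range is shown. Repeat runs of this kind agree to within about two percentage points.

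| City share of variance | Random covariate: centre / city | São Paulo extreme: centre / city |
|---|---|---|
| 0% | 95 / 94 | 94 / 93 |
| 25% | 94 / 94 | 92 / 92 |
| 50% | 92 / 94 | 90 / 93 |
| 100% | 90 / 94 | 82 / 91 |

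**6. Coverage with uncorrected robust standard errors.** Same structure, ICC 0.036 (from the plain mean of 56.6 patients per centre: 2/55.6), 6,000 runs per setting, normal limits.

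| City share | Random covariate: centre / city | Covariate higher in São Paulo and Porto Alegre: centre / city |
|---|---|---|
| 0% | 88.4 / 86.1 | 88.6 / 83.1 |
| 50% | 85.1 / 84.8 | 83.4 / 81.3 |
| 100% | 82.8 / 84.9 | 76.2 / 78.2 |

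Scaling the variance by G/(G − 2) and using t limits is not enough either: at a 50% share it gives 89.8 (centre) against 90.4 (city) for a random covariate, and 88.2 against 87.0 for the second pattern. The city cluster helps only with a correction that works at 16 clusters, such as the jackknife in step 5.

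**The case against.** **The consequence is conditional.** A reader might infer that the intervals are too narrow as a matter of fact. The documents do not support that: they give no within-city correlation, and step 5 shows no loss when the city share is zero. This stands.

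**The city data may not be the centre's city.** Table S2 is not shown. If values follow the patient's residence, they can vary within a centre and the limit of 16 values falls away. The patient-level variables listed in the article include no residence, which favours the centre's city, but that list also refers to Table S2. The condition stands.

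**A city model may never be fitted.** The aims name financial burden, insurance, barriers to drug access and region at macro level, and no city factor. However, the city data are listed under the correlates of medication non-adherence, which is what Aim 2 explores. The point applies to whatever city factors enter a model.

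**The size depends on assumptions.** The ICC puts the whole design effect down to clustering, although equal strata drawn from unequal populations can also inflate it; the residual ICC may be lower. The large shortfalls need most of the variance at city level or an extreme São Paulo value. At a 25% share with a random covariate there is no difference. The 40% assumes equal centre sizes, whereas the article allocates in proportion to centre size. All this stands.

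**The remedy is more than a new cluster identifier.** Step 6 shows that re-clustering alone can do worse than the centre, and 14 df fits only a model with one city covariate. Both are right and shape the fix. It is also true that São Paulo spans two sampling strata. That matters for a stratified variance, but not for a GEE variance summed over cities.

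**Conclusion.** The structural point holds, with a conditional consequence. The stated cluster is the centre; a factor describing the centre's city has at most 16 distinct values across 20 centres; and the planned GEE treats seven co-located centres as independent. Intervals and p-values for such factors will be too narrow if non-adherence remains correlated within a city after covariates.

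At an ICC of about 0.035, coverage of nominal 95% intervals with centre clustering is unaffected at a city share of 0%, about 92% at 50% (90% with São Paulo extreme) and 82% to 90% at 100%. These figures already include a small-sample correction on 20 centres, so when city correlation exists the loss is additional to the general problem of few clusters. Corrected city clustering stays at 91% to 94% throughout and costs almost nothing when there is no city correlation.

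The conclusion rests on city data attaching to the centre's city, equal centre sizes within strata, and the assumed ICC and city share. It is confined to city-level factors in Aim 2.

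**What to change.** For Aim 2 estimates of city-level factors:

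- State that the variance is based on 16 city clusters, and keep centre clustering for the other factors.
- Use a small-sample correction suited to so few clusters, for example a delete-one-city jackknife or a bias-reduced sandwich. A delete-one-city jackknife can be applied to the planned model without changing its point estimates.
- Take t limits whose degrees of freedom reflect 16 clusters and the number of cluster-level covariates in the model: 16 − 2 = 14 with one such covariate, fewer with more.
- Report that results for these factors rest on 16 cities, and state that the values refer to the centre's city. If they refer to the patient's residence, this change needs to be reconsidered.

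No new data are needed. The costs are a city identifier, a corrected variance routine and somewhat wider intervals for the city-level factors.
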